### Secondary outcomes

#### Percentage re-epithelialisation

Clinical photographs will be taken at each dressing change. A panel of experienced burns clinicians will perform a blinded review of the photographs to assess the progress of re-epithelialisation. The burn will be considered healed when 95% re-epithelialised. This method has been used with success in previous studies with primary outcomes of time to re-epithelialisation [27, 36].

#### Pain and distress

Pain and distress will be assessed at home between dressing changes via parents and patients and during dressing changes in clinic via clinicians. Parents and patients will rate their pain based on an age-appropriate scale. Patients aged 3–8 years old will self-report pain intensity using the Faces Pain Scale Revised (FPS-R), a validated scale for paediatric pain assessment. The main benefit is that it demonstrates pain in a gender de-identified face whilst conforming to a linear interval scale that children can relate to [37]. Participants over 8 years old will self-report using the 11-point Pain Numerical Rating Scale (P-NRS) (0 to 10). The P-NRS is validated for children > 8 and is easier to use than the FPS-R as it does not require an additional tool [38]. For children of all ages, parents will report their perceived ranking of their child’s pain on an 11-point P-NRS (0 to 10). There is evidence to suggest good correlation between patient and parent assessment of pain, and it is a useful surrogate when a participant score is not able to be ascertained [39].

Clinicians will assess the child’s pain and distress during dressing changes using the face, legs, activity, cry, consolability (FLACC) scale. This is a validated tool for clinicians to assess pain, with evidence suggesting that with experienced burns nurses (which account for the nursing staff at QCH) the accuracy increases [40]. In addition, any analgesic and/or sedative medications administered to the participant at each dressing change will be recorded. This is given in accordance with the pain ladder, where burns that are likely to be larger will receive stronger medication.

#### Itch

Itch will be assessed by parents, participants and clinicians. Parents will rank the perceived itch for children under 5 years using The Toronto Paediatric Itch Scale—a validated, observation-based scale rating itch behaviours on a scale of 0 (absence of itch) to 4 (severe itch with significant disruption). It helps parents to accurately identify itch based on common paediatric itch patterns rather than the patient having to state they are itchy [41]. Parents of children over five will rate their itch on an 11-point Itch Numeric Rating Scale (I-NRS) (0 to 10). Participants aged 5 to 8 years of age will use the validated Itch Man Scale [42], asking patients to identify which picture on a 5-point scale (0–4) best represents their itch. For children over 8 years, a self-reported 11-point I-NRS (0 to 10) will be used. Clinicians will also be asked to rate the perceived itch on an 11-point I-NRS (0 to 10). The requirement for antipruritic medication will be recorded including the dose and number.

#### Scar/skin assessment (at 3 months)

At 3 months following full re-epithelialisation of the burn injury, a face-to-face follow-up will be completed with all participants to conduct a skin and/or scar review. This time point was picked to assess the development of hypertrophic scar formation, requiring 2–3 months [13]. No surgical interventions for scar management will take place between the time of re-epithelialisation and this appointment. Any garments, splints or silicone-based gels required in the interim will be recorded. An ultrasound scan, using BT12 Venue 40 MSK (GE Healthcare) will be taken to measure the thickness of the scar. This is a validated tool for measuring scar thickness and has been utilised in previous studies [43]. Three central images of the scar will be taken (as opposed to peripherally on the scar border) to use in a blinded analysis by clinicians to confirm scar thickness. The Brisbane Burn Scar Impact Profile (BBSIP) will be used to measure the intensity and frequency of sensations such as pain, tightness and discomfort as well as health-related QoL specific to burn scars. This tool is validated for measuring the health-related QoL in children with burn scars [32]. Where a scar crosses a joint, range of motion will be assessed [19].

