A hypertrophic scar is defined as a raised scar above skin level but remains within the margins of injury [13]. These scars usually develop 2 to 3 months post-injury [13] and can be pigmented, hard and thick [14] with a loss of tissue elasticity secondary to an elastin deficiency [15]. An excess of myofibroblast differentiation can ultimately cause tissue contracture [16]. The greatest risk factor for hypertrophic scar formation is prolonged time to wound re-epithelialisation [17]. Risk factors for prolonged re-epithelialisation times include burns that are deeper, more painful, cover larger total body surface areas (TBSA), become infected and have a delayed time to presentation [18]. Hand and foot burns are more painful than burns of other locations [19]. Thus, a deep hand or foot burn with a prolonged time to re-epithelialisation would be considered high risk for hypertrophic scar formation.

Prevention of these scars is imperative as they not only carry a therapeutic burden, they also have significant and sometimes lifelong morbidity [13]. These scars can be functionally restrictive, cosmetically disfiguring, painful and itchy [20]. Fine motor skills may decrease, restricting recreational and vocational pursuits, and self-esteem may drop [21]. Ultimately, these patients may have a decreased quality of life (QoL) with significant psychosocial concerns [22]. One potential way to prevent hypertrophic scar formation is to decrease time to re-epithelialisation through NPWT.

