### Eligibility criteria

Participants will include approximately 30 children that are equal to or less than 16 years of age with a burn that is on the hand or foot (may be in the context of a larger burn and the location of the burn on the hand/foot will be recorded), managed within 24 h of sustaining the injury and is either superficial partial thickness and > 0.5% TBSA on one hand or foot or any sized burn that is deep or full thickness. The patient will be excluded if clinician treatment priority contradicts study enrolment, they do not wish to participate, the child is acutely unwell at the time of presentation or consent is unable to be confirmed within 24 h of sustaining the burn injury (Table 1).

**Table 1 Tab1:** Eligibility criteria

Inclusion criteria	Exclusion criteria
Hand or foot burn, may be in the context of a larger burn	Clinician treatment priority contradicts randomisation
≤ 16 years of age	Do not wish to participate
Managed ≤ 24 h of sustaining a burn injury	Consent unable to be confirmed within 24 h of sustaining burn injury
Superficial partial thickness burn ≥ 0.5% TBSA on one hand or foot	The child is acutely unwell at the time of presentation
Any sized burn that is deep partial or full thickness	TBSA > 10%

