### Blinding

Due to the nature of the study, double blinding will not be possible as both the treating clinicians and the participant will be aware of the treatment modality. Even if NPWT were to be applied to all participants but blinded to whether the intervention has been turned on, it is evident when looking at the dressing what treatment group the participant is in. It will be possible however to blind the clinicians to some of the secondary outcomes. Time to re-epithelialisation will be calculated based on when a blinded panel of clinicians deem photographs of the wound to be 95% re-epithelialised. Similarly, scar thickness will be measured based on three blinded ultrasound photographs. In addition, to minimise bias based on observation of wound re-epithelialisation, any surveys or questions regarding the patient’s progression will be asked of staff/patients before the dressings are removed.

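### Ultrasound scar thickness at 3 months has no described unburned-skin reference, so it carries native skin thickness as noise and is hard to read as scar elevation

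*Protocol article*

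**What the plan says.** The section on scar/skin assessment at 3 months says that an ultrasound scan "will be taken to measure the thickness of the scar" and fixes the image set: "Three central images of the scar will be taken (as opposed to peripherally on the scar border) to use in a blinded analysis by clinicians". The Blinding section gives the same derivation: "scar thickness will be measured based on three blinded ultrasound photographs". Neither section describes an image of unburned skin, or a difference or ratio to normal skin.

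The purpose of the visit is stated in the same section: "This time point was picked to assess the development of hypertrophic scar formation". The Introduction says what that condition is: "A hypertrophic scar is defined as a raised scar above skin level but remains within the margins of injury".

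Eligibility covers "children that are equal to or less than 16 years of age with a burn that is on the hand or foot". There is no lower age limit, and the Intervention section has a suction band for children under 6 months, so infants are expected. Site within the hand or foot is not restricted, but "the location of the burn on the hand/foot will be recorded".

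Randomisation is stratified by hand versus foot and by theatre versus ED. Data analysis plans linear regression for continuous outcomes, with the stratification variables as covariables where appropriate. Neither age nor palmar/plantar versus dorsal site is named.

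**The concern.** The condition of interest is defined relative to the surrounding skin, but the measurement is thickness at the centre of the scar. Without a reference, that thickness is native skin plus any excess. Two children can give the same reading, one with a flat healed burn on thick skin and the other with a raised scar on thin skin.

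Native thickness differs by age and between palm or sole and dorsum. That is general anatomy and is not stated in the documents. The trial admits the full range of both. At stake are the precision of the mean difference in a small sample and the ability to interpret the result, in millimetres, as scar elevation.

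**Working it through.** **The plan's own figure.** The plan gives none for scar thickness. The half-widths in the Sample size section concern enrolment, treatment received and loss, and have no bearing here.

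**Inputs from the protocol.** There are 30 children, about 15 per arm. The tolerated loss of up to 40% leaves 30 × 0.6 = 18, or 9 per arm.

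**Inputs assumed, because the documents give no thickness data.**
- Native thickness has a between-child SD s of 0.3, 0.5 or 0.8 mm.
- Excess is half-normal with scale 0.5 mm, so its SD is 0.5 × √(1 − 2/π) = 0.301 mm (variance 0.0909).
- A reference scan recovers native thickness with error SD 0.15 mm (variance 0.0225).
- Native thickness and excess are independent and add.

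**Formulas.** The SE of the arm difference is SD × √(2/n), with n per arm.
- Without a reference: SD = √(s² + 0.0909).
- Scar minus reference: SD = √(0.0909 + 0.0225) = 0.337 mm. The native part cancels.

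**Results.** √(2/15) = 0.365 and √(2/9) = 0.471.

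| Native SD (mm) | SD, no reference | SE, 15 per arm | SE, 9 per arm | Ratio to SE with reference | Native share of variance |
|---|---|---|---|---|---|
| 0.3 | 0.425 | 0.155 | 0.200 | 1.3 | 50% |
| 0.5 | 0.584 | 0.213 | 0.275 | 1.7 | 73% |
| 0.8 | 0.855 | 0.312 | 0.403 | 2.5 | 88% |
| With reference | 0.337 | 0.123 | 0.159 | 1.0 | – |

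**Scale-free check.** Let r be native SD divided by excess SD, and suppose a perfect reference. The loss factor is then √(1 + r²). In units of the excess SD, with 15 per arm, the 95% CI half-width is 0.75 with the reference. Without it, the half-width is 0.84, 1.06, 1.35 or 1.67 at r = 0.5, 1, 1.5 or 2.

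**Where the gain stops.** Differencing replaces s² by the squared reference error. If that error were as large as the native SD (0.3 mm against s = 0.3 mm), nothing would be gained.

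**Effect of covariates already planned.** The s in the table is best read as the native SD left after adjustment. If the hand/foot term lowered it from 0.5 to 0.3 mm, the ratio would fall from 1.7 to 1.3.

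**Price of two extra covariates.** If k added terms explain nothing, the expected variance factor is (N − 3)/(N − 3 − k). With k = 2 it is 15/13 = 1.15 at N = 18 (SE about 7% larger) and 27/25 = 1.08 at N = 30 (SE about 4% larger).

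**The case against.** - **The article is condensed.** It never calls the analysed value absolute, and the full protocol may contain a reference scan. That remains possible. But the article gives the number, position and use of the images, and no unburned site is among them. If a reference scan exists, one sentence settles the matter.
- **Ultrasound is described as validated for scar thickness.** So it is, but a valid measure of thickness is not thereby a measure of height above skin level.
- **Native thickness is partly handled.** Hand versus foot is a stratification factor and may enter the model, and burn location is recorded. This stands and reduces the loss. It does not separate palm or sole from dorsum, or infants from adolescents.
- **The additive model and the near-perfect reference favour the remedy.** This also stands. Deep partial and full-thickness burns are eligible, and nothing in the documents supports simple addition for them.
- **The outcome is secondary and unpowered, with no formal testing.** The visit also includes a clinical scar review, the BBSIP and, where a scar crosses a joint, range of motion. This stands and limits the weight of the point.

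A reader might infer four stronger conclusions, which the documents do not support:
- *The arm comparison is biased.* Randomisation balances native thickness in expectation.
- *Site and age dominate the value.* At an assumed native SD of 0.3 mm, native skin is only about half the variance.
- *Children put in the wrong order of scarring would distort a result.* The plan compares arm means and ranks no individuals.
- *The SD would mislead the sizing of the later trial.* Nothing says that scar thickness will size it, and a trial using the same measure would need this same SD.

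**Conclusion.** The point holds as one of precision and interpretation. As described, the 3-month thickness value mixes native skin with any excess, whereas the protocol's definition of hypertrophic scar concerns only elevation. The mean difference between arms remains a fair comparison, but it is noisier than necessary and cannot readily be read as scar height.

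The size of the loss is unknown from the documents. Under the assumptions above, the SE is about 1.3 to 2.5 times that obtained with a reference, less to the extent that hand/foot adjustment already absorbs native variation. No stated figure is wrong, and no primary conclusion changes. It is an optional to moderate improvement to an exploratory outcome.

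**What to change.** **Minimum.** State that the scar-thickness model will adjust for age and for burn location, coded palmar/plantar versus dorsal. This needs no new data, provided location is recorded at that level. It uses one or two degrees of freedom in about 18 to 30 children.

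**Preferred, in addition.** At the same visit and on the same machine, take images of matched unburned skin: the same site on the other limb or, if both were burned, adjacent skin of the same aspect. Analyse scar thickness with the reference as a covariate, or analyse the difference. The covariate form is safer because it does not force the reference to count one for one, which matters if the additive picture fails in deeper burns. The cost is a few more images per child and their blinded reading, with no extra visit.

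If a reference scan is already part of the full protocol, a sentence saying so and naming the analysed quantity is enough.

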#### Cost analysis

A record of the resources and associated cost (costed at market rate) for each participant will be recorded. This will include treatment costs (e.g. the number of dressing changes, type and size of dressings used, scar therapy products) as well as other burn-related resources (and costs) that may be important to a health service deciding which of the interventions to implement in their burn care model. Number of admissions, length of stay, number of operations and clinic appointments will be recorded and costed at hospital projections (i.e. price of hospital bed per night, hourly theatre rate). Labour time (e.g. occupational therapists, physiotherapist, nurses and surgeons) will be quantified for each patient (on the basis of time duration utilised and number of appointments required) and costed at the relevant state award rates for each respective discipline. This data will be recorded with each presentation to hospital.

### Sample size

This is a pilot study. It is primarily designed to determine whether NPWT is a feasible, acceptable and safe intervention in paediatric hand and foot burns given the apprehension of use in this cohort in our previous trial. This study is not powered to achieve statistical significance for secondary outcomes. This pilot study will enrol 30 participants to determine feasibility, safety and acceptability of the proposed intervention. There is minimal relevant literature to base expected outcomes on; sample size has therefore been based off the recommendations of Whitehead et al. [44], Birkett and Day [45] and Browne [46]. Recruiting 30 participants will enable us to estimate the percentage of eligible participants who enrol to within ± 11% (assuming 90% will enrol), the percentage of intervention group participants who receive treatment to within ± 18% (assuming 87% will receive treatment) and the number lost to follow-up, withdrawn or ineligible to within ± 15% (assuming 20% loss), all with alpha = 0.05.

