### Trial design

This study is a parallel-group, two-armed, single-centre, pilot, randomised trial contrasting the outcomes of burns patients treated with (1) standard dressings of Mepitel® and ACTICOAT™ (approximately 15 patients, control) against (2) standard dressings plus a NPWT RENASYS TOUCH™ device (approximately 15 patients, intervention). An overview of the study design is summarised in the Standard Protocol Items: Recommendations for Interventional Trials (SPIRIT) figure (Fig. 1) and the SPIRIT checklist (Supplement 1).

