### Outcomes

#### Pilot trial primary outcomes

Previous acute paediatric burn RCTs have shown that theoretical frameworks for feasibility are often unachievable [27, 29–32]. Given the specificity of the type of burn (significant hand and/or foot burns), it is likely that eligible participants will form a small subcohort. In addition, dropout rates may be higher for the 3-month follow-up especially if there is no scar and the only reason to attend the appointment is for research purposes. Therefore, for this study, a modified feasibility framework has been developed based on the guidelines of Polit and Beck [33] (Table 2). If at the completion of this trial the results are inconclusive or have raised further questions, this study will help guide the feasibility parameters of a larger study.

**Table 2 Tab2:** Study feasibility parameters

Nil minimum screening rate
Greater than or equal to 80% of eligible participants will agree to enrol
Greater than 80% of participants in the intervention groups will receive their allocated treatment (measured twice weekly whilst participant recruited to study)
Less than 10% of data collection for primary outcomes will be missing
Less than or equal to 40% of participants will be lost to follow-up, withdraw from the study or be deemed ineligible after they have commenced treatment

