### Data analysis

Continuous data will be summarised as either mean (standard deviation) or median (interquartile range) depending on distribution, whilst categorical data will be summarised as frequency (percentage). Feasibility outcomes will be presented descriptively as frequency and percentage. Data will be compared between-groups using linear regression (continuous outcomes), logistic regression (binary outcomes) or Poisson regression (count outcomes). In all cases, treatment group will be included as a fixed effect in the analysis model. Stratification variables will be included as covariables when appropriate. The assumptions for each model will be tested, and if model assumptions are not met, comparisons will be made using non-parametric methods. The effect estimates for each model will be presented as mean difference (continuous outcomes), odds ratio (binary outcomes) and incidence rate ratio (count outcomes), although with 95% confidence intervals. The between-group difference between binary outcomes may also be presented as an absolute difference when appropriate. There will be no formal statistical hypothesis testing.

When the outcome variable is measured repeatedly, for example pain, we will use multilevel mixed effects models to account for the likely non-independent of the repeated measures from each participant. In these situations treatment group and time will be included as fixed effects, with a group-by-time interaction.

An intention-to-treat analysis is preferred as it compares all subjects in the groups to which they were originally randomly assigned (despite withdrawal, treatment failure or cross-over). However, we will also conduct per protocol analyses to assess the potential effect of complying to treatment.

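### The three ± margins in the sample-size section are normal approximations that pass 100% in two cases and understate the unfavourable side in all three, and the stated reporting of feasibility percentages carries no interval

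*Protocol article*

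**What the plan says.** The Sample size section gives the purpose as "This pilot study will enrol 30 participants to determine feasibility, safety and acceptability of the proposed intervention". It takes the number from cited recommendations on pilot trials and then describes what that number delivers, for three percentages:

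- enrolment: "to estimate the percentage of eligible participants who enrol to within ± 11% (assuming 90% will enrol");
- treatment received in the NPWT arm: "the percentage of intervention group participants who receive treatment to within ± 18% (assuming 87% will receive treatment");
- loss, withdrawal or ineligibility: "the number lost to follow-up, withdrawn or ineligible to within ± 15% (assuming 20% loss").

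The sentence closes with "all with alpha = 0.05". The Trial design section puts "approximately 15 patients, intervention" in the NPWT arm.

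Table 2, under Pilot trial primary outcomes, sets the cut-offs: at least 80% enrolment, "Greater than 80% of participants in the intervention groups will receive their allocated treatment", and no more than 40% loss.

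On reporting, the Data analysis section says "Feasibility outcomes will be presented descriptively as frequency and percentage". The 95% confidence intervals in that section belong to the effect estimates of the between-group models.

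**The concern.** Taken literally, 87% ± 18% ends at 105% and 90% ± 11% at 101%. A margin that passes 100% shows that the approximation behind it has broken down. When it does, the true interval is lopsided: short towards 100% and long towards the middle of the scale. For enrolment and treatment received, the long side is the one facing the 80% cut-off, so a symmetric margin flatters the design where it matters. For loss, the long side runs upwards, towards the 40% cut-off.

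The reporting rule adds to this. The article describes what its size achieves through the precision of three percentages, then plans to show those percentages without any measure of precision. With 15 children, 13 is the smallest count above 80% (12/15 is exactly 80%), and 13/15 is the assumed 87%. Shown alone it reads as a pass, although the data would be compatible with a true rate of about 60%.

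**Working it through.** **Inputs.** n = 30 enrolled; n = 15 in the NPWT arm (Trial design); assumed rates 90%, 87% and 20%, and alpha 0.05 (Sample size). The article does not say whether alpha is one- or two-sided; I take it as two-sided, so z = 1.96.

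**Step 1: reproduce the stated margins.** The Wald half-width is z·√(p(1−p)/n).

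- Enrolment: 1.96·√(0.90·0.10/30) = 10.7 points
- Treatment received: 1.96·√(0.87·0.13/15) = 17.0 points (17.2 at 13/15)
- Loss: 1.96·√(0.20·0.80/30) = 14.3 points

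Rounded up to whole points these are 11, 18 and 15, as stated.

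**Step 2: the ranges they imply.** 90 ± 11 = 79–101%; 87 ± 18 = 69–105%; 20 ± 15 = 5–35%. The first two pass 100%; the third is possible.

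**Step 3: intervals suited to small counts.** Exact is Clopper-Pearson. Wilson is [p + z²/2n ± z·√(p(1−p)/n + z²/4n²)] / (1 + z²/n). For 13/15 the Wilson terms are (0.9947 ± 0.2145)/1.2561, giving 62.1–96.3%.

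| Quantity | Count | Implied by the article | Exact 95% | Wilson 95% |
|---|---|---|---|---|
| Treatment received | 13/15 | 69–105% | 59.5–98.3% | 62.1–96.3% |
| Enrolment, 30 as denominator | 27/30 | 79–101% | 73.5–97.9% | 74.4–96.5% |
| Enrolment, about 33 approached | 30/33 | 79–101% | 75.7–98.1% | 76.4–96.9% |
| Loss | 6/30 | 5–35% | 7.7–38.6% | 9.5–37.3% |

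**Step 4: the enrolment denominator.** The quantity is a percentage of eligible families, and 30 is the number who enrol, so it is the numerator. At 90% uptake, 30/0.90 ≈ 33 would be approached, which is why 30/33 is the better row.

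**Step 5: the shortfall on the side facing the cut-off.**

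- Treatment received, lower limit: 69 − 62.1 = 6.9 points (Wilson) to 69 − 59.5 = 9.5 points (exact)
- Enrolment, lower limit: 79 − 76.4 = 2.6 to 79 − 75.7 = 3.3 points with 30/33; 4.6 to 5.5 points with 27/30
- Loss, upper limit: 37.3 − 35 = 2.3 to 38.6 − 35 = 3.6 points

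**Step 6: does any position relative to Table 2 change?** For treatment received and enrolment, the lower limit is below 80% both as stated (69%, 79%) and as recomputed. For loss, the upper limit is below 40% both ways. No position changes.

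**The case against.** The best defence is that nothing here was miscalculated and nothing turns on it. The margins follow from a standard formula, and rounding up is cautious. The 30 comes from cited pilot recommendations, so the margins describe the size and did not generate it. The stated ranges already dip below 80%, so a careful reader is warned. On the enrolment denominator, using 33 would shrink the Wald margin to 10.2 points, so 11 errs slightly on the safe side. Finally, the article is condensed, its reporting sentence does not forbid intervals, and a SAP could add them.

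Much of this stands. It means the point concerns stated precision and reporting and leaves the size of the trial alone. It does not rescue ranges that end at 105% and 101%, or lower limits several points too high. On reporting, the article does more than stay silent: it names the form of presentation for feasibility outcomes and, in the same section, attaches confidence intervals to other estimates. That fits poorly with a size described by precision.

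Three stronger readings are tempting, and the documents do not support them.

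- A reader might infer an arithmetic slip, because 17.0 and 14.3 would normally be rounded to 17 and 14. Rounding up gives all three stated figures.
- A reader might infer that no result in 15 children could place the 95% lower limit above 80%. For 15/15 the two-sided limit is indeed 78.2% (0.025^(1/15); Wilson 79.6%), but the one-sided limit is 0.05^(1/15) = 81.9%, and the article does not state sidedness.
- A reader might want the safety conclusion capped in advance at an upper limit of about 20%. That presumes zero events before any data exist. The Safety/harm section grades events from minor deviations upwards, so zero cannot be assumed, and a pilot need not give a precision figure for every objective.

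**Conclusion.** The point holds for the stated precision and for the reporting rule. Two of the three implied ranges pass 100%, and all three are too narrow on the side facing the cut-off: by about 7 to 9.5 points for treatment received, about 3 points for enrolment with 33 approached (about 5 with 27/30), and about 2 to 4 points for loss. The cause is the choice of approximation. The reporting sentence then leaves out the precision by which the size was described.

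This rests on two-sided 95% limits, 15 children in the NPWT arm, the article's own assumed rates turned into whole counts, and 33 approached at about 90% uptake. The sample size and the position of each interval relative to Table 2 are unaffected.

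**What to change.** In Sample size, replace the three ± margins with exact or Wilson 95% intervals, and name the method. With exact limits these are 59.5–98.3% for treatment received (13/15), 75.7–98.1% for enrolment (30/33) and 7.7–38.6% for loss (6/30). Say that the enrolment denominator is the number of eligible families approached.

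In Data analysis, add that each Table 2 percentage, and the proportion of children with any adverse event in each arm, is reported with an exact or Wilson 95% confidence interval.

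The cost is a few sentences and a few extra columns in the results tables. No more patients are needed. The downside is that the stated precision looks less favourable.
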